### 2.4.3. Built-in “Safety Switch”

iNKT cell-based approaches have already been shown to have a reasonable safety profile ([Kunii 2009](#), [Motohashi 2006](#), [Yamasaki 2011](#)), even when iNKT cells are administered in the chronic viral infection setting (hepatitis B virus, hepatitis C virus trials; [Field 2017](#)).

### 2.4.4. Corticosteroid Use and iNKT Cells

Based on recently published data ([RECOVERY 2020](#)), high-dose steroid treatment (dexamethasone) is now considered standard of care for patients with the severe COVID-19 infection.

It is unknown whether use of steroids, or other agents with immunosuppressive activity, could impact the immunostimulatory effect of iNKT cells.

However, in patients with later-stage COVID-19, where immunopathology drives disease, the immunosuppressive benefits of dexamethasone on pro-inflammatory cytokines is complementary, not contraindicated for combination use with iNKT cell therapy. Glucocorticoids have been investigated in preclinical and clinical settings of coronaviruses and have most recently demonstrated reductions in the mortality of patients on ventilators. The underlying benefit attributed to the potent anti-inflammatory action of glucocorticoids is through inhibition of pro-inflammatory cytokines (interleukin [IL]-1, tumor necrosis factor, and IL-6), chemokines, and other soluble mediators (such as prostaglandin E2, leukotrienes and histamine) that act on the vasculature to promote vasodilation and leukocyte recruitment ([Bowles 2002](#), [Cain 2020](#)). Treatment with agenT-797 (iNKT cells) may augment known anti-inflammatory effects of glucocorticoids by further reducing levels of IL-1 and IL-6 ([Hu 2009](#)).

While there are limited data related to the impact of glucocorticoids on immunologic mechanisms in the development of COVID-19 pathology(ies), data suggest that dexamethasone in combination with lenalidomide in patients with multiple myeloma may be used safely, in combination with immune therapies, and have no deleterious impact on iNKT cells. Importantly,

patients with multiple myeloma treated with lenalidomide and dexamethasone showed an increase in natural killer cell frequency ([Lee and Lim 2016](#)). In addition, steroids have been used in combination with chimeric antigen receptor T cells (CAR-T) therapy, with no differences observed relative to CAR-T proliferation/expansion in either high cumulative dose or low cumulative dose steroid administration settings ([Topp 2019](#)).

## **2.5. CONCLUSIONS**

iNKT cells have natural antiviral roles and are known to traffic to the lungs. Their potential for improving both short-term and long-term immunity provide a compelling rationale for their exploitation in SARS-CoV-2 and influenza.

## **2.6. STARTING DOSE RATIONALE**

In this study, an administered dose range of 100 to  $1000 \times 10^6$  iNKT cells will be explored. In an autologous iNKT cell clinical trial, patients received 3 doses every 2 weeks of iNKT cells (range of 15 to 220 million cells per dose) with no significant toxicities ([Exley 2017](#)). In other allogeneic cell therapy trials with related cell populations such as NK and cytokine-induced killer cells ([McGeer 2007](#), [Miller 2005](#), [Laport 2011](#)), study dosing began with modest initial doses of 100,000 cells/kg, which then escalated to 20 million cells/kg and then to 100 million cells/kg ([McGeer 2007](#), [Miller 2005](#), [Laport 2011](#)). These ranges are consistent with the proposed dose levels for agenT-797.

Using highly pure iNKT cells (> 95%) at the 3 doses proposed, prospective toxicities are further minimized by keeping levels of trace contaminating T cells to a minimum ([Fuchs 2012](#)). Indeed, iNKT cells actively suppress graft-versus-host-disease (GVHD) while maintaining antitumor activity providing further rationale for safety and potential clinical activity ([Mavers 2017](#)). Taken together these findings suggest that, even with cell therapies capable of expansion in vivo, half-log dose escalation schemes provide a safe and supported low initial dose providing for more rapid escalation to potentially more efficacious doses, within the study.

### 3. TRIAL OBJECTIVES AND ENDPOINTS

| Primary Objectives                                                                                                                                                                                                                                                           | Primary Endpoints                                                                                                                                                                                                                                                                                                                                                                                                                                                                                                                                                                                                                                                                                                                                                                                                                        |
|------------------------------------------------------------------------------------------------------------------------------------------------------------------------------------------------------------------------------------------------------------------------------|------------------------------------------------------------------------------------------------------------------------------------------------------------------------------------------------------------------------------------------------------------------------------------------------------------------------------------------------------------------------------------------------------------------------------------------------------------------------------------------------------------------------------------------------------------------------------------------------------------------------------------------------------------------------------------------------------------------------------------------------------------------------------------------------------------------------------------------|
| 
 
To assess safety and tolerability of agenT-797 infusion
 
                                                                                                                                                                    | 
 
Number and severity of adverse events (AEs) and dose-limiting toxicities (DLTs) at evaluated dose levels
 
                                                                                                                                                                                                                                                                                                                                                                                                                                                                                                                                                                                                                                                                               |
| Secondary Objectives                                                                                                                                                                                                                                                         | Secondary Endpoints                                                                                                                                                                                                                                                                                                                                                                                                                                                                                                                                                                                                                                                                                                                                                                                                                      |
| 
 
To assess evidence of improvement and resolution of ARDS following infusion with agenT-797
 
To assess avoidance of multiorgan dysfunction syndrome
 
                                                                 | 
 
Assessment of ventilator-free days
 
Time to extubation
 
Time to intubation in patients with moderate ARDS
 
Vital signs and physical examination findings
 
Lung injury score (LIS): The LIS is a composite 4-point scoring system including the PaO2/FiO2, positive end-expiratory pressure (PEEP), quasi-static respiratory compliance, and the extent of infiltrates determined by imaging
 
Intensive care unit-free days
 
Mean daily sequential organ failure assessment score(s)
 
Supportive interventions used (e.g., use of prone ventilation, paralytics, pulmonary vasodilators, and other interventions affecting oxygenation)
 
All-cause mortality rates within 30 days and at 6 months
 
 |
| 
 
To assess evolution of cytokine release syndrome (CRS)
 
                                                                                                                                                                     | 
 
Change in clinical parameters and biomarkers relevant to CRS (D-dimers, ferritin, C-reactive protein, IL-1, and IL-6)
 
                                                                                                                                                                                                                                                                                                                                                                                                                                                                                                                                                                                                                                                                  |
| 
 
To assess decay in quantitative (as feasible, or positive/negative) viral burden from upper and lower respiratory tract samples collected sequentially, as appropriate
 
To assess prevention of viral reactivation
 
 | 
 
Decay in quantitative (as feasible, or positive/negative) viral burden from upper and lower respiratory tract samples collected sequentially under treatment
 
Time from dosing to viral clearance and determining if iNKT cells prevent re-activation of other viruses (cytomegalovirus, human papillomavirus, herpes simplex virus, Epstein-Barr virus) and fungal infections
 
                                                                                                                                                                                                                                                                                                                                                                                                 |
| Exploratory Objectives                                                                                                                                                                                                                                                       | Exploratory Endpoints                                                                                                                                                                                                                                                                                                                                                                                                                                                                                                                                                                                                                                                                                                                                                                                                                    |
| 
 
To identify biomarkers that could predict clinical activity against severe acute
 
                                                                                                                                           | 
 
Additional cytokine signatures and laboratory values, including, but not limited to, levels of
 
                                                                                                                                                                                                                                                                                                                                                                                                                                                                                                                                                                                                                                                                                         |

|                                                                                                                                                                                 |                                                                                                                                                                                                                                                                                                                                                      |
|---------------------------------------------------------------------------------------------------------------------------------------------------------------------------------|------------------------------------------------------------------------------------------------------------------------------------------------------------------------------------------------------------------------------------------------------------------------------------------------------------------------------------------------------|
| respiratory syndrome-coronavirus 2 (SARS-CoV-2)                                                                                                                                 | interferon gamma, lactate dehydrogenase, tumor necrosis factor alpha, prothrombin time, partial thromboplastin time, and creatine phosphokinase, change with treatment, and if change is correlated with clinical improvement                                                                                                                        |
| 
 
To evaluate persistence and longevity of allogeneic iNKT cells agenT-797 with respect to tissue localization in target organs
 
 | 
 
Presence and number of iNKT cells and other immune cells in bronchoalveolar lavage and/or microlavage fluid
 
Persistence of allogeneic iNKT cells in circulation through direct measurement in peripheral blood and through cell free DNA as surrogate of general persistence in tissue(s)
 
 |
| 
 
To evaluate development of alloimmunity against administered donor cells
 
                                                      | 
 
Presence of alloantibodies to major histocompatibility (MHC) Class I and MHC Class II and rate of mismatch
 
                                                                                                                                                                                         |
| 
 
To evaluate whether iNKT cells prevent secondary infections
 
                                                                   | 
 
Presence of iNKTs cells in peripheral blood and risk of secondary infections (e.g., Pseudomonas aeruginosa, Klebsiella pneumoniae, and fungal infections)
 
                                                                                                                            |
| 
 
To evaluate whether iNKT cells improve lung fitness through assessments of respiratory function
 
                               | 
 
Clinical and respiratory function assessments
 
Change in pulmonary involvement based on X-ray and/or computed tomography (CT) scans, as available
 
Health of lung epithelial cells (RNA analysis)
 
                                                                                  |
| 
 
To explore whether iNKT cells promote viral resolution without lung fibrosis in SARS-CoV-2 (COVID-19) patients
 
                | 
 
Time from dosing to viral clearance
 
Fibrosis signs based on X-ray and/or CT scans and respiratory function assessments
 
                                                                                                                                                                    |

## 4. INVESTIGATIONAL PLAN

### 4.1. OVERALL STUDY DESIGN

This is a Phase 1/2 study to evaluate the safety and potential efficacy of agenT-797, an unmodified, allogeneic iNKT cell therapy, in patients with moderate to severe ARDS secondary to SARS-CoV-2 or influenza, either with intubation or at high risk to be intubated, as determined by the Berlin definition ([ARDS 2012](#)).

**Completed:** Part 1 will employ a standard 3+3 dose escalation design of agenT-797. All patients will receive a single infusion of agenT-797. Patients will also receive other treatments and supportive care per discretion of the Principal Investigator. Once the maximum tolerated dose (MTD) of agenT-797 has been cleared in Part 1, an Expansion Cohort will be opened. A Safety Monitoring Committee (SMC) will be established to assess safety and decide on escalation to

next cohort and expansion dose, as well as any protocol modification to include less severe cases.

**Part 2 (Expansion)** of the study will evaluate an additional cohort in up to 15 patients:

- Cohort 4 – patients with moderate to severe ARDS secondary to SARS-CoV-2 or influenza, according to Berlin definition, who are on mechanical intubation

The SMC will continue to review safety.

The number of patients in each cohort is presented in [Table 2](#).

**Table 2: Cohorts for agenT-797**

| Cohort | Number of Patients | Escalation Type | agenT-797 level          |
|--------|--------------------|-----------------|--------------------------|
| 1      | 3-6                | 3+3             | $100 \times 10^6$ cells  |
| 2      | 3-6                | 3+3             | $300 \times 10^6$ cells  |
| 3      | 6+                 | 3+3             | $1000 \times 10^6$ cells |
| 4      | Up to 15           | 3+12            | $1000 \times 10^6$ cells |

## 4.2. NUMBER OF PATIENTS

It is estimated that up to approximately 43 patients, requiring or at risk of needing mechanical ventilation with moderate to severe ARDS, per the Berlin definition ([ARDS 2012](#)), will be enrolled into the study. Additional patients may be added at the discretion of the SMC based on the review of the totality of the data including safety and efficacy data.

## 4.3. TREATMENT ASSIGNMENT

This is an open-label, single-arm study. Patients will receive a single dose of agenT-797. Each patient will stay on the dose level and schedule assigned at trial entry. No randomization and blinding procedures will be applied to treatment assignments.

## 4.4. STAGGERED COHORT ENROLLMENT

Each cohort will have a minimum of 3 patients enrolled. agenT-797 (Cohort 1) will be administered in the first patient, and treatment will be administered to the next patient 7 days after the last patient was administered agenT-797. Cohort 2 will be administered 14 days after the last patient was dosed in Cohort 1 and will follow the staggered dosing in Cohort 1 (every 7 days/patient). If patients tolerate low dose (Cohort 1) and intermediate dose (Cohort 2) treatment with agenT-797, Cohort 3 may be enrolled after 14 days.

An additional cohort in up to 15 patients will be evaluated:

- Cohort 4 – patients with moderate to severe ARDS secondary to SARS-CoV-2 or influenza, according to Berlin definition, who are on mechanical intubation

## **4.5. DOSE ESCALATION CRITERIA**

A SMC will assess safety, decide on appropriateness of dose escalation, and define the expansion cohort dose.

### **4.5.1. Dose-Limiting Observation Period**

A minimum of 3 patients will be enrolled in each cohort, and the DLT observation period will be 14 days for each patient. Patients will continue to be monitored post-DLT period throughout the study. The totality of the safety data will be factored in by the SMC in the decision-making to move to enrollment of Cohort 2.

If a DLT occurs in 1 of the 3 patients during the DLT period, the cohort will be expanded to a total of 6 patients; if a DLT occurs in  $\geq 2$  patients in the total cohort of 6 patients, the MTD will be deemed to be exceeded, and that dose will not be escalated. The prior dose level will be evaluated to then proceed into the Expansion Cohort. The interval between patients in each cohort is at least 7 days with a 14-day interval between each cohort ([Section 4.4](#)).

The dose of agenT-797 will be escalated if none of the first 3 evaluable patients enrolled has a DLT based on SMC evaluations of data. If a cohort was expanded to include a total of 6 evaluable patients and no DLT occurs in the additional 3 patients, then the dose will be escalated based on the SMC evaluation of data.

After Amendment 7, the SMC will monitor safety on an ongoing basis.

### **4.5.2. Maximum Tolerated Dose**

If a DLT occurs in  $\geq 2$  patients in a cohort, the MTD will be deemed to be exceeded, and the prior dose level will be evaluated to determine the MTD by increasing enrollment to 6 patients. If the prior dose level was already deemed to be safe and enrolled 6 patients, then it will be defined as the MTD. Dose Escalation will continue until the MTD is reached or the maximum planned dose level is shown to be safe. If none of the first 3 evaluable patients enrolled at the maximum planned dose experience a DLT, an additional 3 patients may be enrolled for a total of 6 patients at the maximum planned dose. Additional patients may also be enrolled in other lower dose cohorts.

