### **9.2. SAMPLE SIZE**

The total sample size is expected to be up to approximately 43 evaluable treated patients. Since the study uses 3+3 design with 3 dose levels, up to 18 patients may be needed in Dose Escalation part (Part 1). Additional patients will be enrolled to the Expansion Cohort. Please refer to the SAP for details. A matched control may be used to complete the comparative analysis. This will be defined in the SAP.

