### 3.7 Maximum Tolerated Dose

If a DLT occurs in  $\geq 2$  patients in a cohort, the MTD will be deemed to be exceeded, and the prior dose level will be evaluated to determine the MTD by increasing enrollment to 6 patients. If the prior dose level was already deemed to be safe and enrolled 6 patients, then it will be defined as the MTD. Dose Escalation will continue until the MTD is reached or the maximum planned dose level is shown to be safe. If none of the first 3 evaluable patients enrolled at the maximum planned dose experience a DLT, an additional 3 patients may be enrolled for a total of 6 patients at the maximum planned dose. Additional patients may also be enrolled in other lower dose cohorts.

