| 
 
To assess safety and tolerability of agenT-797 infusion
 
                                                                                                    | 
 
Number and severity of adverse events (AEs) and dose-limiting toxicities (DLTs) at evaluated dose levels
 
                                                                                                                                                                                                                                                                                                                                                                                                                                                                                                                                                                                                                                                                                  | 
 
Frequency of AEs and affected patients at evaluated dose levels
 
                                                                                                                                                                                                                                                                                                                                                                                                                                                                                                                                                                                                                        |

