#### **4.11.2.4 All-case mortality**

Proportion of death from all causes within 30 days and at 6 months and its 95% score CI will be calculated. It is a direct measurement of efficacy of the therapy.

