#### 4.11.6 Dose-Limiting Toxicity

The following summaries will be generated based on the DLT analysis set by dose level and overall:

- A summary of the number and proportion of patients who experience a DLT during the DLT evaluation period.
- A summary of the number and proportion of TEAEs experienced by patients during the DLT evaluation period.

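### The primary DLT proportion is planned without a confidence limit, while the results that clear the top dose (0/3, 0/6 or 1/6) leave exact upper limits of 63%, 39% and 58%

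*Combined protocol and SAP*

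**What the plan says.** Protocol 4.5.2 and SAP 3.7 give the end of escalation in the same words: "Dose Escalation will continue until the MTD is reached or the maximum planned dose level is shown to be safe". Neither section attaches a number, an acceptable DLT rate or a confidence limit to the second condition.

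The numerical criteria are in protocol 4.5.1 (SAP 3.6). The dose "will be escalated if none of the first 3 evaluable patients enrolled has a DLT based on SMC evaluations of data". Also, "If a DLT occurs in 1 of the 3 patients during the DLT period, the cohort will be expanded to a total of 6 patients". Should the three added patients have no DLT, the dose again passes, subject to SMC evaluation. Two or more DLTs mean that the MTD is exceeded.

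On cohort size at the top dose, after 0/3 "an additional 3 patients may be enrolled for a total of 6 patients at the maximum planned dose" (SAP 3.7; same text in protocol 4.5.2). Protocol Table 2 and SAP Table 1 plan six or more patients for Cohort 3.

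On reporting, SAP 4.11.6 plans, by dose level and overall, "A summary of the number and proportion of patients who experience a DLT during the DLT evaluation period". The primary estimator in SAP Table 2 is "Frequency of AEs and affected patients at evaluated dose levels". Neither mentions an interval. For mortality, SAP 4.11.2.4 says: "Proportion of death from all causes within 30 days and at 6 months and its 95% score CI will be calculated". SAP 4.11.2.11 gives the secondary-infection proportion a 95% score interval as well. SAP 4.2 sets a display format for Wilson intervals and suppresses percentages for zero counts.

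**The concern.** The safety conclusion is the main product of this study, and its dose-finding component will rest on very few patients. In samples of three or six, a low DLT count is compatible with a wide range of true rates. A reader can judge that only if the proportion comes with its limit. The SAP already uses a suitable method for two other proportions but does not assign it to the DLT rate.

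The undefined phrase in 4.5.2 adds to the problem. If it carries over into the study report, a dose that met a 3+3 criterion will be described in terms that the data cannot support. Two of the three clearing results do not exclude DLTs in more than half of patients.

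**Working it through.** **Stated figure.** Protocol 9.2 gives up to 18 patients for Part 1: 3 dose levels × 6 = 18, which reproduces. The documents state no target DLT rate, power or operating characteristic.

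**Clearing results** (from 4.5.1 and 4.5.2). These are 0/3 if the cohort stops there; 1/3 then 0/3, which is 1/6; and 0/3 followed by three more patients with at most one DLT, which is 0/6 or 1/6. A result of 1/3 alone does not pass; it triggers expansion.

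**Upper limits on the DLT rate.** The exact (Clopper-Pearson) one-sided 95% limit for zero events in n is 1 − 0.05^(1/n). For 1/6 it is the p that solves (1−p)^6 + 6p(1−p)^5 = 0.05. The Wilson column is the upper end of the two-sided 95% interval.

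| Result | Exact one-sided 95% | Wilson |
|---|---|---|
| 0/3 | 63% | 56% |
| 0/6 | 39% | 39% |
| 1/6 | 58% | 56% |

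**Chance of clearing a dose at true DLT rate p**

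- Cohort may stop at 0/3: (1−p)^3 + 3p(1−p)^2 × (1−p)^3.
- Six always enrolled, at most one DLT: (1−p)^6 + 6p(1−p)^5.

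At p = 1/3, the first is 0.2963 + 0.4444 × 0.2963 = 0.428. The second is 0.0878 + 0.2634 = 0.351. The rate of 1/3 is my assumption, so I show a range:

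| Assumed p | May stop at 0/3 | Always six |
|---|---|---|
| 25% | 60% | 53% |
| 30% | 49% | 42% |
| 1/3 | 43% | 35% |
| 40% | 31% | 23% |

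**Effect of more patients at the same dose.** Cohorts 3 and 4 both receive 1000 × 10^6 cells. Taking the minimum of six in Cohort 3 and the maximum of 15 in Cohort 4 gives 6 + 15 = 21. The exact one-sided limit is then 13% for 0/21 and 21% for 1/21.

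**Denominator.** Two points are unsettled. After 0/3, the text makes the next three patients optional, while the cohort tables plan six or more. Protocol 4.5.1 and 8.1.4 and SAP 3.6 use a 14-day DLT period, while the DLT analysis set in SAP 4.5 requires 28 days. A patient observed for 14 days but not 28, with no DLT, counts towards the escalation decision but falls outside the set used for the reported rate.

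**The case against.** The strongest reply is that the plan is descriptive and the safety judgement does not rest on 4.5.2 alone. SAP 3.2 and 4.11.1 rule out formal testing. Each escalation decision depends on SMC evaluation. Protocol 4.5.3 adds separate stopping criteria and review of toxicities after day 14. Cohort 4 adds up to 15 patients at the top dose to study safety further. Part 1 is marked completed, so rewording 4.5.2 changes no escalation decision. All of this stands. It limits the point to reporting and wording. It does not remove it: a confidence limit is itself descriptive, the SAP uses intervals elsewhere, and SMC review puts no bound on the reported rate.

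Some stronger readings are tempting and should be resisted.

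- *The plan declares a dose safe on 0 or 1 DLT in 3 to 6 patients.* No section says so. The clearing results are inferred from 4.5.1, and 1/3 is not among them. Counting 1/3 as a pass would give 0.2963 + 0.4444 = 74% at a rate of 1/3, which is not this design.
- *43% is the plan's error rate.* It needs an assumed rate of 1/3 and a cohort that stops at 0/3. Two DLTs in six is a trigger on an observed count, not a stated unacceptable true rate. Under the planned size of six or more, the six-patient calculation gives 35%. Supplementary Table S2 lists 13 patients in Cohort 3, so the cohort did not end at three.
- *The DLT rate is the only endpoint without an interval.* The median duration of oxygenation intervention (SAP 4.11.2.2) and the median time to viral clearance (SAP 4.11.2.10) have none either.
- *A bare 0% would be printed.* SAP 4.2 suppresses percentages for zero counts, so the table would show a count. It would still show no limit.

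**Conclusion.** The point holds as one about missing precision and an overstated phrase in the primary safety result. The clearing results leave exact upper limits of 63%, 39% and 58%, and the SAP plans no limit for them. The chances of clearing are ordinary 3+3 behaviour, not a miscalculation and not a reason to fault the choice of design. They rest on assumed true rates, on independent patients with a common DLT rate, and on SMC review not overriding the count. The upper limits need no assumed rate, but they need a defined denominator, which the documents do not yet give. The change is worth making before results are reported, because it governs what the primary result can claim.

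**What to change.** 1. In SAP 4.11.6 and the primary row of SAP Table 2, report the DLT proportion by dose level with either a Clopper-Pearson one-sided 95% upper limit or the Wilson interval already provided for in SAP 4.2. Name one method. Pool Cohorts 3 and 4 at 1000 × 10^6 cells and also show each cohort, since Cohort 4 is restricted to intubated patients. Show the limit for zero counts too, as an exception to the suppression in SAP 4.2.
2. Word the safety conclusion from that limit, stating which DLT rates are excluded. Describe the top dose as cleared under the 3+3 rule with the MTD not exceeded, in place of the undefined phrase in protocol 4.5.2 and SAP 3.7.
3. Reconcile the optional three patients in protocol 4.5.2 and SAP 3.7 with the six or more in protocol Table 2 and SAP Table 1. Reconcile the 14-day DLT period with the 28-day DLT analysis set. The sponsor must decide which passages govern; the aim here is only a defined denominator.

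The cost is one extra table column, some changed wording and a less favourable stated safety conclusion. No extra patients are needed. Protocol 9.5 already allows changes to the analysis to be documented in an amendment, the final SAP or the clinical study report.
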